## Objectives

Considering the lack of linguistic diversity in datasets with a clear bias towards English (13, 36) and social media data (24), we see an urgent need for further non-English speech datasets (37). To this day there is no sufficiently large German speech corpus from severely ill psychiatric patients. There have been several valuable efforts to advance the analysis of language in the context of psychotherapy and mental health within German-speaking populations. However, existing studies have primarily focused on outpatient samples with milder symptom severity (38) or relied on relatively small datasets (39). While these contributions are undoubtedly significant, they nevertheless leave an important gap regarding large-scale datasets from more severely affected patients in inpatient settings. Existing corpora, such as the Research and Teaching Corpus of Spoken German (FOLK) (40), are not specifically designed to meet the needs and peculiarities of psychiatric and psychotherapeutic contexts, thus limiting their utility for NLP and multimodal methods in these fields. Even from a global perspective, language data sets are rather rare compared to the multitude of existing languages (41).

We therefore aim to generate a large enough trans-diagnostic collection of audio data of hospitalized patients and patients treated in our outpatient clinic. A study by Parola et al. (42) has shown several language specific differences regarding reduced semantic coherence in schizophrenia, which indicates a limited generalizability of speech patterns across different languages.

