With our study, we aim to fill this gap by applying recent advances in NLP and multimodal methods. Our goal is to help identify non-explicit content language patterns in clinical patients, which can serve as prognostic markers specifically for the German language. Thus, our primary aim is to assess the suicide risk in patients with depression, bipolar disorder, and psychotic disorders, such as schizophrenia, schizoaffective disorder and acute polymorphic psychotic disorder (according to ICD-10), as well as the psychopathological development (Clinical Global Impression, CGI). As a secondary outcome we want to assess the overall psychopathological condition of the patients. This includes standardized and validated questionnaires comprising the clinician's impression of the patients general psychosocial functioning (Global Assessment of Functioning, GAF), suicidal symptoms (Depressive Symptom Index—Suicidality Subscale, DSI-SS) and suicidality (Suicidal Scale of the Mini-International) as well as electronic health records (EHR) of the patient's psychopharmacological medication. Generally, the standardized text of the patient's EHR will be accessible for the text-based analysis. These will be supplemented by the standardized assessment through a clinician, which will be used as the gold standard for comparison with the AI analysis.

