### Eligibility criteria

We will include patients with ICD-10 diagnoses F20.x, F23, F25, F30-33, aged between 18 and 65 years, who are legally competent, without any issues in voice production, and have a German speaking proficiency of at least B2 (lower level in German would contain too little information content of linguistic utterances). Additionally, psychotherapists employed at the University Hospital Frankfurt will be included for the therapeutic conversations.

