### Recruitment

The participants are recruited from both inpatient and outpatient individuals at the Department of Psychiatry, Psychosomatics, and Psychotherapy at the University Hospital Frankfurt. Additionally, a physician collects data at the [name] Clinic in Königstein. For ongoing enrollment, patients will be screened regularly for participation criteria by the study teams and by their treating clinicians. Study information will be given by members of the study team who are not involved with the patient's treatment to prevent participation out of a sense of obligation and to maintain voluntary participation. There will be no assignment of interventions since participation does not include differing intervention types.

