
## Statistical methods

### Statistical methods for primary and secondary outcomes

We will employ a zero-shot prompting approach with OpenAI's recently released GPT-OSS (Generative Pretrained Transformer—Open Source Software) series models, which are available under the permissive Apache 2.0 license and have demonstrated strong performance on reasoning tasks relevant to clinical assessment. We have selected these models for several methodological and practical reasons:

First, their open-weight nature ensures full transparency and reproducibility of our analyses. Second, their mixture-of-experts architecture enables efficient deployment on clinical infrastructure with limited computational resources. Third, their documented performance on complex reasoning tasks, including healthcare-related queries, makes them well-suited for psychiatric assessment applications.

Our primary analytical comparison will involve two model sizes from the GPT-OSS family: GPT-OSS-120B (116.8 billion total parameters with 5.1 billion active parameters per token) and GPT-OSS-20B (20.9 billion total parameters with 3.6 billion active parameters per token) (58). This comparison directly addresses a critical question for clinical deployment: whether larger, more capable models provide sufficient performance advantages to justify their greater computational demands, or whether smaller, more efficient models can achieve comparable diagnostic accuracy. The GPT-OSS-120B model has been shown to achieve near-parity with state-of-the-art reasoning models on standard benchmarks while running efficiently on a single 80GB GPU, whereas GPT-OSS-20B delivers comparable performance to advanced compact models while requiring only 16GB of memory, making it feasible for deployment on standard clinical workstations or even edge devices.

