For each model size, we will systematically evaluate two distinct inference configurations defined by the temperature hyperparameter, which controls the randomness of model outputs. We will test a conservative configuration (temperature = 0.1) designed to prioritize consistency and clinical reliability by producing more deterministic responses, and a rather liberal configuration (temperature = 0.8). In the NLP literature the effects of temperature are well represented but systematic clinical applications have yet to be done to our knowledge. Accuracy in multiple choice question answering tasks show high consistency in temperature ranging between 0 and 1, but an expansion to other problem types is recommended (59). This strategic selection of hyperparameters reflects the clinical tension between reproducibility critical for diagnostic applications where consistency across assessments is paramount and the risk of highly inconsistent outcomes that could potentially lead to incorrect diagnoses and treatment recommendations. In addition, we apply top-p (nucleus) sampling with a cumulative probability threshold of 0.9 to each analysis. This setting restricts sampling to the smallest set of tokens whose cumulative probability mass is at least 0.9, balancing output diversity with coherence.

This yields a 2 × 2 factorial design with four experimental conditions: 1. GPT-OSS-120B with temperature 0.1, 2. GPT-OSS-120B with temperature 0.8, 3. GPT-OSS-20B with temperature 0.1, and 4. GPT-OSS-20B with temperature 0.8. We will evaluate each condition's performance on primary outcomes including general diagnostic classification accuracy and suicidality detection, severity score prediction (correlation with standardized clinical measures), and clinical utility metrics such as sensitivity, specificity, and positive/negative predictive values. All model versions, hyperparameters, and inference code will be fully documented and made available to ensure complete reproducibility.

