Tier 1: Unimodal Baseline Analysis. We will analyze each modality independently to establish baseline predictive performance before considering fusion. For the text modality, we will conduct two-way mixed-effects logistic regression with outcomes (diagnostic classification or severity degree) regressed on the fixed effects of model size and temperature, with random intercepts for participant and session. Effect sizes will be reported as odds ratios with 95% confidence intervals. For the acoustic modality, we will conduct mixed-effects linear regression using a reduced set of the most clinically relevant acoustic features selected *a priori* based on prior literature associations with depression and suicidality, including pitch variability, energy measures, MFCC and jitter as predictors of continuously scored clinical outcomes (e.g., severity scores from standardized rating scales) (60, 61).Tier 2: Factorial Interaction Analysis for 2 × 2 Design. For text-based predictions, we will formally test the 2 × 2 factorial design using mixed-effects ANOVA to partition variance according to main effects (model size, temperature) and their interaction. Specifically, we will model primary outcome (e.g., predicted depression severity) as a function of fixed effects for model size (GPT-OSS-120B vs. 20B), temperature (0.1 vs. 0.8), and their interaction (Model Size × Temperature), with random intercepts for participants and sessions to account for the hierarchical data structure. This approach allows us to determine whether inference strategy recommendations (conservative vs. liberal temperature) can be applied consistently across model sizes, or whether optimization differs by model choice. If a significant Model Size × Temperature interaction emerges, it would suggest that clinical deployment requires model-specific tuning. Conversely, absence of interaction would support unified recommendations applicable regardless of computational constraints. We will report partial eta-squared (*η*²p) effect sizes with 95% confidence intervals for each factorial term.Tier 3: Multimodal fusion and Late-Fusion Integration. To evaluate how textual and acoustic information combine for clinical prediction, we will employ a structured late-fusion approach. For each of the four 2 × 2 factorial conditions, we will generate separate predictions from the GPT-OSS models (text modality) and from a logistic regression model trained on acoustic features (acoustic modality). We will then integrate these predictions through weighted averaging, with weights determined via cross-validation (80% training, 20% held-out validation) on a stratified subset of sessions. This approach maintains interpretability—each modality's contribution can be quantified—and avoids the architectural complexity that would introduce uncontrolled hyperparameter flexibility incompatible with pre-registration.We will quantify multimodal benefit by comparing fusion performance (AUC, sensitivity/specificity at clinically relevant decision thresholds) against the best unimodal baseline. If fusion provides incremental improvement beyond single modalities, we will use mixed-effects logistic regression with interaction terms to test whether the fusion benefit depends on model size or temperature setting. This tests the hypothesis that acoustic information provides complementary information that enhances text-based predictions uniformly, or whether certain model configurations better leverage multimodal information.

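### Suicidality performance is scored across mixed diagnoses with no within-diagnosis metric and no diagnosis-only benchmark, so it cannot be separated from recognition of the diagnosis

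*Protocol article*

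**What the plan says.** **Sample.** The Objectives section intends to "generate a large enough trans-diagnostic collection of audio data of hospitalized patients" and outpatients, and states that "our primary aim is to assess the suicide risk in patients with depression, bipolar disorder, and psychotic disorders". Under Eligibility criteria: "We will include patients with ICD-10 diagnoses F20.x, F23, F25, F30-33, aged between 18 and 65 years". Participants are "recruited from both inpatient and outpatient individuals" (Recruitment). No quota per diagnosis is given.

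**Outcomes and metrics.** The section Statistical methods for primary and secondary outcomes scores each of the four model conditions on "primary outcomes including general diagnostic classification accuracy and suicidality detection", with sensitivity, specificity and predictive values. AUC appears in Tier 3, for fusion.

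**Models.** For text, "We will employ a zero-shot prompting approach". In Tier 1 the text outcomes are "regressed on the fixed effects of model size and temperature, with random intercepts for participant and session"; Tier 2 adds the interaction of size and temperature. The acoustic models hold acoustic features only. Tier 3 fits an acoustic logistic regression and the fusion weights on study data, and compares fusion with the best single-modality result.

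Diagnosis is recorded at t1 (Table 1), but no reported metric, model or comparator uses it as a stratum, term or benchmark.

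**The concern.** A pooled AUC counts pairs of sessions from different diagnosis groups. If suicidality is more frequent in one group, a score that merely ranks sessions by group wins more than half of those cross-group pairs without distinguishing suicidal from non-suicidal sessions inside any group. Pooled sensitivity and specificity behave the same way.

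The plan gives reason to expect such a signal. Recognising the diagnosis is itself a primary outcome, and the acoustic feature set was chosen because its markers are associated with psychiatric conditions.

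At stake is what the result means. The treating clinician already knows the diagnosis, so performance that comes from it adds nothing to a risk assessment. With pooled metrics alone, a reader cannot tell how much performance is left once diagnosis is set aside.

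**Working it through.** **1. The plan's own figure.** The Sample size section gives n = 162, critical values 68 and 94, actual alpha 0.0491726 and actual power 0.8046757. An exact two-sided binomial test of p = 0.50 that rejects at X ≤ 68 or X ≥ 94 with n = 162 gives alpha 0.0491726, and power 0.8046757 at p = 0.50 + 0.11 = 0.61. The figure reproduces, so the study is sized to detect an accuracy of 0.61 against 0.50.

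**2. What a diagnosis-only rule needs to reach 0.61.** Take the plan's balanced proportion of 0.5 and assume equal shares of affective and psychotic sessions. Calling every affective session suicidal and every psychotic session not suicidal has accuracy 0.5·pa + 0.5·(1 − pp). With assumed prevalences pa = 0.61 and pp = 0.39 (a 22-point gap), this is 0.305 + 0.305 = 0.61.

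**3. Pooled AUC of a diagnosis-only score.** Inputs are assumptions, not in the documents: 50% depressive, 15% bipolar and 35% psychotic sessions, suicidality taken as yes/no, and the prevalences in the table. Groups are ranked by prevalence:

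AUC = Σ P(group | suicidal) × [P(lower-prevalence group | not suicidal) + 0.5 × P(same group | not suicidal)]

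Worked case, prevalences 50/30/15%:
- Suicidal: 0.25 + 0.045 + 0.0525 = 0.3475, so the group shares are 0.719, 0.129, 0.151.
- Not suicidal: 0.25 + 0.105 + 0.2975 = 0.6525, so the shares are 0.383, 0.161, 0.456.
- AUC = 0.719 × (0.161 + 0.456 + 0.192) + 0.129 × (0.456 + 0.080) + 0.151 × 0.228 = 0.686 (from unrounded shares).
- Flagging all depressive sessions: sensitivity 0.719, specificity 1 − 0.383 = 0.617.

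| Prevalence dep/bip/psy (%) | Gap dep − psy (points) | Pooled AUC | Sens / spec, flag depressive | Accuracy of that rule | Accuracy of always answering not suicidal |
|---|---|---|---|---|---|
| 30/30/30 | 0 | 0.50 | 0.50 / 0.50 | 0.50 | 0.70 |
| 35/30/25 | 10 | 0.556 | 0.569 / 0.531 | 0.5425 | 0.6925 |
| 40/25/20 | 20 | 0.615 | 0.650 / 0.567 | 0.5925 | 0.6925 |
| 50/30/15 | 35 | 0.686 | 0.719 / 0.617 | 0.6525 | 0.6525 |
| 60/30/10 | 50 | 0.756 | 0.789 / 0.677 | 0.72 | 0.62 |

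The AUC of this score within any one diagnosis is 0.50 in every row, by construction.

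**4. Check with two groups (affective against psychotic).** Here AUC = (sensitivity + specificity)/2. With an affective share of 0.5, prevalences of 40/30% give 0.555, 40/20% give 0.619, 50/20% give 0.665, 60/20% give 0.708 and 60/10% give 0.775. With a share of 0.7 the same pairs give 0.545, 0.594, 0.630, 0.668 and 0.712. The range agrees with step 3.

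**5. Price of a within-diagnosis AUC.** Take 200 interviews (Sample size), the assumed mix, and prevalences of 50/30/15%. Suicidal × non-suicidal pairs in the same diagnosis: 50 × 50 + 9 × 21 + 10.5 × 59.5 = 2500 + 189 + 625 = 3314. All pairs: 69.5 × 130.5 = 9070. So 1 − 3314/9070, about 63%, of the pairs drop out, and 2500/3314, about 75%, of the remainder are depressive. The bipolar stratum has 30 sessions, about 9 of them suicidal; at up to five sessions per patient, these could come from as few as 6 patients.

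**The case against.** **The article is silent rather than wrong, and strata may be in a fuller plan.** This has some weight: nothing says that the metrics will be computed only on pooled sessions. But the article does fix its metrics, model terms and fusion comparator, and presents them as guarding against later methodological flexibility. On those terms, a within-diagnosis analysis added later would depart from the stated plan. The one mention of stratification concerns choosing the fusion weights, names no variable and does not stratify a reported result.

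**Pooled performance is a legitimate target.** This stands. The corpus is meant to be trans-diagnostic, and performance across that mixture is a fair thing to estimate. A reader might infer that the pooled figure is biased upwards. The documents do not support that; the figure answers a different question from detection of suicidality within a diagnosis.

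**The size is unknown.** This also stands. A reader might infer that a model recognising only the diagnosis will certainly score well above chance. That needs prevalence gaps which the documents do not give; with equal prevalences the AUC is 0.50. On plain accuracy the rule often gains nothing: it equals the majority answer at 50/30/15% (0.6525 each) and falls below it at 40/25/20%. No figure supports extending the argument to inpatient or outpatient setting, or to severity scores.

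**The text models are zero-shot.** True: they cannot learn the association from study labels and could bring it only as prior knowledge. The acoustic model and the fusion weights can learn it directly.

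**Conclusion.** The point holds in conditional form. As written, the plan cannot separate suicidality detection from diagnosis recognition, because it has neither a within-diagnosis metric nor a diagnosis-only comparator. Under the assumed mix of 50/15/35%, the pooled AUC available from diagnosis alone runs from 0.50 with equal prevalences, through about 0.55 with a 10-point gap and 0.62 to 0.69 with gaps of 20 to 35 points, to 0.76 with 50 points. A two-group calculation with other shares gives a similar range. Where the trial falls in it depends on prevalences that only its own data will show. Exposure is greatest for the acoustic and fusion models. This should be settled before analysis, since it changes what the trial can conclude about speech as a marker of suicidality.

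**What to change.** Keep the pooled figures and add two results beside them for suicidality:

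- **Same-diagnosis AUC.** Compute it only from pairs of sessions in the same group (depressive F32-33, bipolar F30-31, psychotic F20/F23/F25), with intervals clustered by patient.
- **Diagnosis-only benchmark.** Score the same sessions from the diagnosis group alone, and report the same metrics. State in advance that the text, acoustic and fusion models must exceed it before pooled performance is attributed to detecting suicidality from speech.

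**Cost.** A short addition to the analysis text and a few lines of code; diagnosis is already collected at t1. The within-diagnosis AUC will have clearly wider intervals (about 63% of pairs dropped under the assumed mix), will be weighted mostly towards depressive patients, and the bipolar stratum will be descriptive only. For that reason it should accompany the pooled figure, not replace it.

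Adding diagnosis and setting as fixed effects to the mixed models would not solve this. It leaves AUC, sensitivity and specificity unchanged. It also hardly moves the size and temperature contrasts, because all four conditions are applied to the same sessions.

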### Outcomes

As part of an initial exploratory analysis, the assessment of psychopathology by treating physicians is to be compared with the evaluation by a computer model. Therefore, using intraclass correlation coefficients or t- tests, the hypothesis “There is no difference in the assessment of patients regarding the severity of illness and suicidality” will be tested.

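### The only metric tied to the primary severity outcome for the four model configurations is correlation, which cannot detect a shift or compression of zero-shot scores

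*Protocol article*

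**What the plan says.** Under *Statistical methods for primary and secondary outcomes*, the article begins: "We will employ a zero-shot prompting approach". It crosses two model sizes with two temperatures and states: "We will evaluate each condition's performance on primary outcomes including general diagnostic classification accuracy and suicidality detection". The same list continues with "severity score prediction (correlation with standardized clinical measures", followed by sensitivity, specificity and predictive values. The type of correlation is not named.

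Two other places bear on severity:

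- The *Outcomes* section opens with this sentence: "As part of an initial exploratory analysis, the assessment of psychopathology by treating physicians is to be compared with the evaluation by a computer model". The method is given as "using intraclass correlation coefficients or t- tests", and the hypothesis is "There is no difference in the assessment of patients regarding the severity of illness and suicidality".
- *Tiers 1 and 2* of the statistical methods: Tier 1 has "outcomes (diagnostic classification or severity degree) regressed on the fixed effects of model size and temperature" in a mixed-effects logistic model. Tier 2 models the predicted severity itself on model size, temperature and their interaction.

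*Data management* defines a gold standard that is separate from the treating physician: an independent psychiatrist, or an experienced assistant in psychiatry, who rates the recordings.

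**The concern.** Whether a model's severity score can stand beside a clinician's rating is a question of agreement and of the size of error. Correlation answers a different question: whether patients are ranked, or linearly ordered, in the same way. A model that rates every patient one point too ill, or that crowds everyone towards the middle of the scale, can correlate as well as one that is on target.

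This matters more for zero-shot models than for fitted ones. A fitted model is pulled towards the reference level by its training data. Here the article describes no calibration step for the text models' severity scores, so an error of level or spread is a foreseeable failure. The metric attached to the outcome would not show it, and two configurations with the same r could have very different errors against the reference.

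**Working it through.** **Is there a figure in the plan to reproduce?** None for severity: the article gives no expected correlation, SD or bias. Its sample size reproduces exactly as a two-sided binomial test of 0.61 against 0.50 (N = 162, critical values 68 and 94, alpha 0.0492, power 0.8047). That is a test of a proportion and has no bearing on the severity metric.

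**Size of the blind spot.** Assumed inputs: rater SD s1 = 1 point, r = 0.80, model SD s2, constant shift d.

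- Concordance coefficient: CCC = 2·r·s1·s2 / (s1² + s2² + d²)
- SD of the differences: sD = √(s1² + s2² − 2·r·s1·s2)
- Mean absolute error (MAE): mean of |N(d, sD²)|, the folded normal

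| Shift d | Model SD s2 | r | CCC | sD | MAE |
|---|---|---|---|---|---|
| 0 | 1 | 0.80 | 1.6/2 = 0.80 | 0.632 | 0.50 |
| 1 | 1 | 0.80 | 1.6/3 = 0.53 | 0.632 | 1.03 |
| 1.5 | 1 | 0.80 | 1.6/4.25 = 0.38 | 0.632 | 1.50 |
| 1 | 0.5 | 0.80 | 0.8/2.25 = 0.36 | 0.671 | 1.04 |

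The column for r does not move. A rank correlation would not move either, because a shift or linear compression preserves order.

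**Would the analysis in the Outcomes section see it?** Constructed data with n = 162 independent pairs, equal SDs and r = 0.80:

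| Shift (SD) | Pearson r | ICC, absolute agreement | ICC, consistency | Paired t |
|---|---|---|---|---|
| 0 | 0.800 | 0.801 | 0.800 | 0 |
| 0.25 | 0.800 | 0.777 | 0.800 | 5.0 |
| 0.5 | 0.800 | 0.712 | 0.800 | 10.1 |
| 1 | 0.800 | 0.534 | 0.800 | 20.1 |
| 2 | 0.800 | 0.267 | 0.800 | 40.2 |

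So the answer depends on a choice that the article leaves open:

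- A paired t-test finds even a 0.25 SD shift: t = 0.25/(0.632/√162) = 5.03. At r = 0.60 the same shift gives t = 3.56, p = 0.0005. Repeated sessions per patient would reduce these values.
- An absolute-agreement ICC falls with the shift. A consistency ICC stays at 0.800 and is as blind to a shift as r.
- With pure compression (d = 0, s2 = 0.5), the mean difference is zero, so the t-test has nothing to detect. The CCC is 0.8/1.25 = 0.64.

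**Would the tiers see it?** Tier 2 has predicted severity as its dependent variable and no reference score in the model. If one configuration scores a point above another on the same sessions, that appears as a main effect or interaction. Which of the two is nearer the clinician does not appear. Tier 1 does not say how severity degree is scored against the reference. Tier 3 reports AUC, sensitivity and specificity of the fused prediction, not error on the severity scale.

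**The case against.** The strongest reply is that severity is not judged by correlation alone in this article. The Outcomes section plans a comparison of model and physician on exactly this question, and either a t-test or an absolute-agreement ICC would expose uniform over-rating. This stands: a reader might infer that no planned analysis could reveal a shift, and the article does not support that. It does not close the gap, for four reasons. The comparison is labelled initial and exploratory. It leaves ICC or t-test, and the ICC form, undecided. It compares with treating physicians rather than with the gold standard in *Data management*. It speaks of one computer model, not of the four configurations.

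A reader might also infer that configurations with equal r would be declared equivalent. The article does not support that either. It plans no equivalence test on r, and Tier 2 would show a difference in level between configurations.

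Three further points deserve weight:

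- Zero-shot does not rule out scale definitions in the prompt, and the prompts are not shown. That a shift will occur is therefore not established, only that it is possible and that the named metric would miss it.
- The deployment question is framed in terms of diagnostic accuracy, and sensitivity and specificity are reported for each condition. Over-rating might surface there as lost specificity, but only if the classifications follow from the same severity judgement, which the article does not say.
- The coefficient type and supplementary error measures may be fixed in a fuller document. But the article does name a metric for this outcome, and as named it does not measure agreement.

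**Conclusion.** The point holds in limited form. Correlation is the only metric attached to the primary severity outcome for the four configurations, and it is exactly invariant to a constant shift or linear compression. The agreement analysis elsewhere could reveal a shift, depending on an unmade choice of method, but it is exploratory and not connected to this outcome. Tier 2 compares configurations with each other, not with the reference.

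The invariance is a mathematical fact and needs no assumption. The size does: at an assumed r of 0.80 and SD of 1 point, shifts of 1 to 1.5 points leave r unchanged, lower concordance to between 0.53 and 0.38, and double to triple the MAE (0.50 to 1.03 and 1.50). With other correlations, a 1 SD shift takes the absolute-agreement ICC from 0.601 to 0.401 (r = 0.60) or from 0.901 to 0.600 (r = 0.90). The documents give no r, SD or bias, so these are illustrations and not forecasts. The point is worth correcting before the analysis. It does not invalidate the design.

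**What to change.** Reconcile the Outcomes section with the list of primary outcomes in the statistical methods, and name the rating that serves as reference for severity. For each of the four configurations, report against that reference:

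- an absolute-agreement ICC or the concordance coefficient, with the form stated;
- mean bias with limits of agreement;
- mean absolute error in scale points.

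Make these the metrics of the severity outcome, with intervals that respect clustering within participant (for example a participant-level bootstrap), since up to five sessions per patient are recorded. Keep correlation as a supplementary figure.

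The cost is analysis wording only, with no new data. The downside is that the reported figures may look less favourable than r.

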Concurrent with text-based analysis using GPT-OSS models, we will extract acoustic features from therapy session recordings using openSMILE (version 3.0) (56) with the eGeMAPSv02 feature set (60), which includes validated markers known to associate with psychiatric conditions. The eGeMAPSv02 feature set comprises 88 acoustic features encompassing spectral (Mel-frequency cepstral coefficients), glottal (fundamental frequency, jitter, shimmer), and prosodic characteristics (energy, speech rate, voice quality measures such as harmonics-to-noise ratio). These features will be extracted at the frame-level (10-millisecond intervals) and subsequently aggregated using statistical functions (mean, standard deviation, minimum, maximum, percentiles) to produce session-level representations comparable to clinical assessment timeframes.

Our overarching analytical strategy employs a three-tier statistical framework designed to characterize how textual, acoustic, and combined modalities contribute to clinical prediction:

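### Tier 1 promises predictive performance for the acoustic modality but names only a regression with no held-out data, so any performance figure from it would be optimistic

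*Protocol article*

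**What the plan says.** All passages are in the protocol article, under statistical methods for primary and secondary outcomes.

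- **Purpose of Tier 1:** "We will analyze each modality independently to establish baseline predictive performance before considering fusion".
- **Acoustic procedure in Tier 1:** "we will conduct mixed-effects linear regression using a reduced set of the most clinically relevant acoustic features". The features are to be chosen in advance from the literature, "including pitch variability, energy measures, MFCC and jitter as predictors of continuously scored clinical outcomes". Their number is not fixed. The pool they come from is larger: "The eGeMAPSv02 feature set comprises 88 acoustic features". The sentence names no subset of sessions, no hold-out, no resampling, no performance measure and no random-effects structure.
- **Text arm:** "We will employ a zero-shot prompting approach". Among the outcomes on which the text conditions are judged is "severity score prediction (correlation with standardized clinical measures").
- **The only data split in the document:** in Tier 3, for the fusion step, "with weights determined via cross-validation (80% training, 20% held-out validation) on a stratified subset of sessions". The acoustic model used there is a separate logistic regression.

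**The concern.** A regression fitted to a set of sessions and then scored on those sessions describes fit. It does not show how well the features predict the score of a new patient. Tier 1 announces the second and, as written, supplies only the first. Coefficients estimated from the outcome always reproduce part of that outcome's noise, so features with no information still yield a positive correlation.

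The text predictions carry no such optimism, because zero-shot prompting estimates nothing from study outcomes. If an acoustic correlation from the Tier 1 fit were printed beside the text correlation, the two would not be on equal terms.

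At stake is the answer to whether voice alone predicts severity. A modest correlation produced by noise could be reported as a weak vocal marker. The same section presents the plan as one that leaves no later freedom of method and that others can replicate directly, so the way the baseline is computed should be fixed before results are seen.

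**Working it through.** **Inputs from the document.** The sample size section requires 162 and plans to collect 200 interviews. The participant timeline allows up to five recorded sessions per participant. Tier 1 names four feature families (pitch variability, energy, MFCC, jitter) out of a pool of 88 features.

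**Inputs that are assumptions.** These are the number of acoustic predictors k (4, 10 and 20 shown), the within-patient correlation of the score (ICC 0.6, varied from 0.3 to 0.8), the ICC of the features (0.6), and the sessions per patient (40 patients × 4 or 81 × 2). A patient random intercept is also assumed.

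**The plan's own figure.** No figure is given for acoustic performance. The 162 used below does reproduce: an exact two-sided binomial test with null proportion 0.5 and alternative 0.5 + 0.11 = 0.61 first reaches 80% power at n = 162, with critical values 68 and 94, alpha 0.04917 and power 0.80468. Dropout of 15% gives 162/0.85 = 190.6, so 191. Dropout of 20% gives 162/0.80 = 202.5, so 203. The planned 200 lies in that range. This only sets n; it does not bear on the point itself.

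**Step 1: expected fit under no signal, independent sessions.** With k uninformative features and n sessions, the expected in-sample R² is k/(n − 1), and r is roughly its square root.

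| k | n = 162 | r | n = 200 | r |
|---|---|---|---|---|
| 4 | 4/161 = 0.025 | 0.16 | 4/199 = 0.020 | 0.14 |
| 10 | 10/161 = 0.062 | 0.25 | 10/199 = 0.050 | 0.22 |
| 20 | 20/161 = 0.124 | 0.35 | 20/199 = 0.101 | 0.32 |

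If all 88 features were used, R² would be 88/161 = 0.547 at n = 162. That is an upper bound only, because the plan specifies a reduced set.

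**Step 2: the same question with repeated sessions.** A random-intercept linear model was fitted by REML to data in which the features are independent of the score (60 data sets per setting, ICC 0.6). Predictions were correlated with the score in two ways: fixed-effect fitted values on the same sessions, and fixed-effect predictions from 5-fold cross-validation with each patient's sessions in one fold.

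| Patients × sessions | k | In-sample r | Left-out patients, r | Left-out patients, R² |
|---|---|---|---|---|
| 40 × 4 | 4 | 0.152 | −0.009 | −0.031 |
| 40 × 4 | 10 | 0.259 | 0.018 | −0.079 |
| 40 × 4 | 20 | 0.344 | 0.002 | −0.184 |
| 81 × 2 | 4 | 0.146 | 0.006 | −0.030 |
| 81 × 2 | 10 | 0.242 | 0.017 | −0.078 |
| 81 × 2 | 20 | 0.330 | −0.034 | −0.213 |

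The simulation agrees with the formula. Left-out patients give the right answer, which is no predictive value.

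**Step 3: sensitivity to the ICC.** With 40 × 4 and k = 10, in-sample r is 0.266 at ICC 0.3 and 0.178 at ICC 0.8. Left-out r is −0.006 and −0.005.

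**Step 4: if patient intercepts entered the predictions.** Each prediction would then use that patient's own scores. Across the settings of Step 2, r would be 0.83 to 0.90, still with no acoustic signal. The plan does not say that it will predict in this way.

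**The case against.** **In-sample scoring is never stated.** Tier 1 names no correlation, R² or error for the acoustic model, and a journal article may leave validation to the full protocol. The first part is true: in-sample scoring is inferred from a predictive purpose paired with a procedure that has no held-out data. But the article is not merely silent. It states what Tier 1 is to deliver, names a method that does not deliver it, and specifies a split elsewhere for another purpose.

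**Tier 1 may be meant as inference.** The text analysis there reports odds ratios for model size and temperature, and the acoustic baseline is listed among the domains for Bonferroni correction. This stands. Tests of coefficients for features chosen in advance would in principle keep their level, and nothing here is directed at them. If inference is all that is meant, the predictive wording does not fit.

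**Tier 1 does not rank the modalities.** This also stands. The text and acoustic models in Tier 1 differ in outcome type and effect measure. The formal comparison is in Tier 3, with a different, logistic acoustic model. A reader might infer that the Tier 1 fit biases the fusion comparison or decides which modality is better. The document does not support that: the Tier 1 mixed model is not itself the AUC comparator.

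**The optimism is limited.** Choosing a reduced set in advance removes data-driven selection among the 88 features. That is right, and with 4 to 10 features the null correlation is modest, at about 0.15 to 0.25.

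**Conclusion.** The concern holds in a limited form. Tier 1 promises predictive performance for voice and, as written, offers only the fit of a regression with no hold-out or resampling. Any r, R² or error read from that fit is optimistic, whereas the text predictions are not fitted to study sessions.

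With about 160 sessions and no acoustic signal, the optimism in r is about 0.15 for 4 features, 0.25 for 10 and 0.35 for 20, against about 0 for left-out patients. These sizes rest on assumed feature counts, an ICC of 0.6 and two to four sessions per patient. At 10 features, an ICC between 0.3 and 0.8 moves the in-sample figure only between about 0.27 and 0.18.

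A reader might infer that uninformative voice features would appear at r near 0.9. That would require patient intercepts in the predictions, which no part of the document plans, so it is a hazard to exclude in the wording and not a property of the plan.

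The point should be fixed, but it does not put the study at risk: it affects neither the sample size nor the data collection.

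**What to change.** State in Tier 1 that the acoustic performance figures (for example correlation and mean absolute error) come from fixed-effect predictions for left-out patients, by repeated K-fold cross-validation with all sessions of a patient in the same fold. Where acoustic and text performance are set side by side, score both on the same sessions and the same outcome. Keep the full-sample mixed model for describing associations, and do not call its fit predictive performance. If Tier 1 is meant only to describe associations, reword its purpose accordingly.

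The cost is a sentence or two in the plan and some extra analysis code. No new data and no added burden on patients are involved. The acoustic figure will probably look less favourable, which is a reason to settle this before results are seen.
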